### Statistical Analysis

All data will be analyzed using RStudio (version 4.3.2; Posit, PBC). Continuous variables (eg, cleft width and bone segment stability score) will be tested for normality using the Shapiro-Wilk test. Depending on data distribution, between-group comparisons will be performed using either the unpaired *t* test (for normally distributed data) or the Mann-Whitney *U* test (for nonparametric data). Categorical outcomes, such as arch form classification (U-shaped, V-shaped, or asymmetrical) and wound healing grades (from the Landry wound healing scale), will be compared using the chi-square test or Fisher exact test, as appropriate.

Longitudinal outcomes (eg, segment stability across time points) will be analyzed using repeated measures ANOVA for normally distributed data or generalized estimating equations for nonparametric repeated measures. All outcome measures will be reported with 95% CIs, and *P*<.05 will be considered statistically significant. Missing data will be handled using multiple imputation, and any potential confounders, such as age or initial cleft width, will be adjusted for using multivariate regression analysis.

To assess the robustness of results, sensitivity analysis will be conducted by comparing results from multiple imputation with complete-case analysis and worst-case scenario imputation.

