### Postoperative Care

All patients will receive antibiotics, analgesics, chlorhexidine mouth rinses, and dietary instructions. Follow-up visits will be scheduled at 1 month, 3 months, 6 months, and 1 year postoperatively.

As this is a prospective observational study, treatment allocation is not randomized. Patients are assigned to either the dentoalveolar transport distraction group or the unilateral Le Fort I advancement group based on specific clinical indications determined by the treating maxillofacial surgeon. Criteria such as cleft morphology, cleft width, presence of adequate bone stock for distraction, soft tissue quality, and anticipated compliance with the distraction protocols are considered during group assignment. To minimize selection bias, all assessments are conducted using standardized protocols, and outcome evaluators are blinded to the intervention type. Additionally, baseline characteristics of both groups will be statistically compared to assess equivalency, and any confounders will be adjusted for during analysis using multivariate regression techniques.

To further minimize allocation bias inherent to the nonrandomized design, we will perform stratified enrollment based on cleft width and age groups. Additionally, a propensity score adjustment will be conducted in the final analysis to balance any observed confounders between groups.

Missing data may arise from loss to follow-up or incomplete clinical or radiographic records. These will be assessed for randomness using the Little missing completely at random test. If data are missing at random, multiple imputation using chained equations will be applied to minimize bias. Variables with >20% missing data will be excluded from the primary analysis but may be used in sensitivity analysis. Potential confounders, such as patient age, cleft width at baseline, and compliance with treatment protocols, will be identified a priori based on clinical relevance and literature review. These variables will be included in multivariate regression models (eg, linear regression for continuous outcomes such as gap width and logistic regression for binary outcomes such as successful closure) to adjust the primary effect estimates. Adjusted effect sizes and CIs will be reported alongside unadjusted comparisons.

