## Results

As of June 2025, patient recruitment, which began in April 2023, is ongoing. Out of 14 intended participants, 12 (85%) have been enrolled (with 7 in the dentoalveolar transport distraction group and 5 in the unilateral Le Fort I advancement group). The enrolled cohort includes 8 male individuals and 4 female individuals, with a mean age of 16.8 (SD 3.9; range 10-23) years. The average cleft width among the participants was 1.5 (SD 0.34; range 1.0-2.1) cm.

Data collection is anticipated to conclude by December 2025, and the results are expected to be published in 2026.

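### A normality pretest on 5 to 7 values per group chooses the unadjusted test for gap width, and the plan does not say whether that test or the planned baseline-adjusted regression decides

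*Protocol article*

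**What the plan says.** The Statistical Analysis section of the protocol article states the rule for continuous measures, giving cleft width as an example: they "will be tested for normality using the Shapiro-Wilk test". The outcome of that check then selects the method: "Depending on data distribution, between-group comparisons will be performed using either the unpaired *t* test (for normally distributed data) or the Mann-Whitney *U* test". The rank test is the choice when normality is rejected. Longitudinal outcomes get a parallel rule: "repeated measures ANOVA for normally distributed data or generalized estimating equations for nonparametric repeated measures".

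Gap closure is a primary outcome (Primary Outcome). It is measured preoperatively, immediately after surgery, and at 1, 3, 6 and 12 months. Seven patients per group are planned (Sample Size Calculation). The Results section reports 12 enrolled, "with 7 in the dentoalveolar transport distraction group and 5 in the unilateral Le Fort I advancement group".

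The article also plans adjustment. The analysis text under Postoperative Care says: "Potential confounders, such as patient age, cleft width at baseline, and compliance with treatment protocols, will be identified a priori". It specifies linear regression for gap width to adjust the primary effect estimates and adds a propensity score adjustment. Statistical Analysis repeats the adjustment for initial cleft width. On the standing of the two kinds of result, Postoperative Care says only: "Adjusted effect sizes and CIs will be reported alongside unadjusted comparisons". The same section lists cleft width among the criteria by which the surgeon assigns patients to a group.

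**The concern.** Two features of the stated rule are weak.

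First, the outcome data choose the method. At 5 to 7 values per group a Shapiro-Wilk test cannot reliably tell a normal from a skewed distribution. The two tests it selects between also address different quantities: a difference in means or a shift in ranks. What is estimated therefore depends partly on chance.

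Second, neither unpaired test, applied to the follow-up gap, takes account of starting width. The planned regression does. Because starting width helps determine who gets which operation, an unadjusted comparison of follow-up gap is open to confounding by design. If the two analyses disagree, the plan gives no rule for which one is the finding.

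**Working it through.** The article states no figure on this point, so there is none to reproduce. The checks below are simulations with the article's group sizes (7/7 planned, 7/5 enrolled). Mann-Whitney is used if either group fails Shapiro-Wilk at 5%; otherwise the t test is used. The article does not say whether the pretest is applied by group or to pooled data; by group is assumed.

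**1. What the pretest detects** (rejection rate per group, 5,000 samples each)

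| True distribution | n=5 | n=7 |
|---|---|---|
| Normal | 0.046 | 0.053 |
| Lognormal, sigma 0.5 | 0.097 | 0.153 |
| Exponential | 0.162 | 0.278 |

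Exponential skew is missed in 1 − 0.278 = 72% (n=7) to 1 − 0.162 = 84% (n=5) of groups. With normal data, the chance that at least one group rejects is 1 − (1 − 0.046)(1 − 0.053) ≈ 0.10 at 7/5 and 1 − (1 − 0.053)² ≈ 0.10 at 7/7.

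**2. Does the pretest change the conclusion?** The verdict depends on it only if the pretest rejects and the two tests also disagree on P<.05.
- Normal data, shifts of 1 to 1.5 SD: the pretest rejects in about 10% of data sets, the tests disagree in about 7 to 9%, and both happen in about 1%.
- Exponential data, same shifts: both happen in about 5 to 8%.
- No true difference: type I error of the two-stage rule is 0.050 to 0.053 (normal) and about 0.047 (exponential).

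**3. Switching between visits, if tests are run at each visit** (the article does not state this). There are five postoperative visits and two groups. With a nominal 5% rejection rate and independent visits, the chance that the chosen test is not the same throughout is about 1 − 0.95^10 = 0.40. Simulated with between-visit correlation of 0 to 0.8, it is 0.36 to 0.40 for normal data.

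**4. Unadjusted test against baseline-adjusted model.** Baseline SD is 0.34 cm (Results). Chance alone gives a between-group baseline difference with SE 0.34 × √(1/7 + 1/7) = 0.18 cm at 7/7 and 0.34 × √(1/7 + 1/5) = 0.20 cm at 7/5, a 95% range of about ±0.36 to ±0.39 cm. Selection by width would add to this.

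Assume a true baseline imbalance of 1 SD (0.34 cm), no treatment effect, and baseline-outcome correlation ρ. The unadjusted comparison is then biased by ρ × 1 SD. At ρ = 0.7 and 7/7 the expected t statistic is about 0.7/√(2/7) = 1.31 instead of 0. Type I error, 8,000 data sets per setting:

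| ρ (assumed) | t test, 7/7 | t test, 7/5 | Adjusted model |
|---|---|---|---|
| 0.3 | 0.080 | 0.075 | 0.047–0.049 |
| 0.5 | 0.142 | 0.122 | 0.050–0.052 |
| 0.7 | 0.231 | 0.194 | 0.050–0.053 |

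Allowing for simulation error, this is about 7 to 24% for the t test and about 5% for the adjusted model.

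**5. Precision.** Adjustment cuts residual variance by ρ²: 0.5² = 25% to 0.7² = 49%. With no baseline imbalance and an assumed 1.5 SD effect, power (t test, then adjusted model) is 0.73 and 0.73 at ρ = 0.3, 0.73 and 0.80 at 0.5, and 0.73 and 0.93 at 0.7, all at 7/7. At 7/5 it is 0.65 and 0.64, 0.65 and 0.71, and 0.64 and 0.85.

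**The case against.** The strongest reply is that the article already contains the remedy. It names baseline cleft width as a confounder and commits to linear regression of gap width. A reader who sees only the t test and Mann-Whitney options might infer that preoperative width is ignored; the article does not support that. What stands is that the adjusted and unadjusted results are unranked. A t test on change from baseline would also use starting width, though with a slope fixed at 1, and the article does not say whether follow-up gap or change is tested.

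A reader might also infer that the pretest inflates false positives or often decides the primary result. Step 2 shows otherwise. The t and Mann-Whitney tests do disagree more often than the verdict changes, but that disagreement exists whichever test is chosen.

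Visit-by-visit testing is an inference from the measurement schedule; the article sends longitudinal outcomes to repeated measures ANOVA or GEE. Counting the preoperative visit would raise the switching figure to about 1 − 0.95^12 = 0.46, but that visit is not a treatment comparison.

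It is also fair that the baseline-outcome correlation may be low. Distraction continues until the gap closes, so later gaps may be near zero whatever the starting width. Both the bias and the precision gain would then shrink.

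Finally, an article may leave the choice of deciding model to an analysis plan that is not shown, and normality pretesting is common practice. That would excuse silence. Here the article states a data-driven rule and states that both results are reported, so the comment concerns what is written.

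**Conclusion.** The point holds in a limited form. The article fixes a data-dependent choice of test that does not do its job at 5 to 7 patients per group, and it leaves that test level with an adjusted regression that should take precedence. The pretest alone does little damage, for the reasons in step 2.

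The main reason to change is confounding by starting width. The false-positive risk of about 7 to 24% for the unadjusted t test rests on two assumptions not found in the article: a 1 SD baseline imbalance and a correlation of 0.3 to 0.7. With less imbalance or a weaker correlation it moves towards 5%. Greater precision cannot be promised: there is none at a correlation of about 0.3. Adjusting for starting width also does not remove confounding by the other assignment criteria, such as bone stock or soft tissue quality.

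**What to change.** Remove the Shapiro-Wilk step as a rule for choosing the test. State that gap closure is decided by the linear model already planned, with CBCT gap as outcome and group and preoperative CBCT gap as terms, at one named visit (for example 12 months). Label the unadjusted comparison as supportive and fix its form in advance. A permutation P value from the same model is optional if clustering of gaps near zero is a worry.

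The required measurements are already scheduled. The cost is a few sentences and one degree of freedom for the covariate. The change should be made before outcomes are compared between groups.

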### Secondary Outcomes

The secondary outcomes assessed in this study will include the following:

Stability of the advanced or transported segment: evaluated by bidigital palpation and CBCT and graded on a 5-point bone stability scale (1=highly unstable; 5=highly stable).Soft tissue healing: evaluated by the Landry wound healing scale at all times of follow-up and graded from 1 (very poor) to 5 (excellent).

All outcome assessments will be performed by evaluators who are blinded to the treatment group. CBCT scans will be anonymized, coded, and randomized before analysis. In cases where unblinding may occur (eg, visible hardware on radiographs), a second independent blinded reviewer will reassess.

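### Landry healing grades are ordered but are tested with chi-square or Fisher, which costs power at 12 to 14 patients; separately, GEE is mislabelled as nonparametric and needs a small-sample correction

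*Protocol article*

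**What the plan says.** Secondary Outcomes defines two parallel five-grade scales. Landry soft tissue healing is "graded from 1 (very poor) to 5 (excellent", and segment stability is "graded on a 5-point bone stability scale (1=highly unstable; 5=highly stable". Both are ordered.

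Statistical Analysis treats them differently. Landry grades share a list with a nominal outcome: "Categorical outcomes, such as arch form classification (U-shaped, V-shaped, or asymmetrical) and wound healing grades". The tests for that list are fixed in the same sentence: "wound healing grades (from the Landry wound healing scale), will be compared using the chi-square test or Fisher exact test". The stability score sits in another list: "Continuous variables (eg, cleft width and bone segment stability score) will be tested for normality using the Shapiro-Wilk test", after which the choice is an unpaired t test or Mann-Whitney.

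For repeated measurements, with segment stability as the example, the plan is repeated measures ANOVA if the data look normal and otherwise "generalized estimating equations for nonparametric repeated measures". No variance estimator, reference distribution or model terms are given.

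Sample Size Calculation plans 14 patients, 7 per group. Results reports 12 enrolled so far, "with 7 in the dentoalveolar transport distraction group and 5 in the unilateral Le Fort I advancement group". The significance level is 5%.

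**The concern.** There are two separate problems, with different consequences.

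**Landry grades.** Chi-square and Fisher give the same P value if the grade columns are shuffled. They therefore cannot tell a steady move from poor towards excellent from a scatter with no direction. With two groups and five grades there are up to 10 cells, an average of 14/10 = 1.4 or 12/10 = 1.2 patients each. The study can hardly afford to discard the order. The scale is listed as secondary, but soft tissue healing is also named in the study hypothesis (Introduction) and in the Primary Objective.

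**GEE.** It needs a mean model and a link, so it is semiparametric, and its usual standard errors rely on many independent subjects. Here there are 12 to 14. A five-point score is an obvious candidate for the non-normal branch, so the fallback may well be used.

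**Working it through.** The article states no power or error rate for these analyses, so there is no plan figure to reproduce. The sample size rests on a binary facial-esthetic success rate.

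**Inputs from the article.** Five ordered grades; group sizes 7:7 (planned) and 7:5 (enrolled); two-sided 5%; four follow-up visits ("Follow-up visits will be scheduled at 1 month, 3 months, 6 months, and 1 year postoperatively"), or five assessments counting the one immediately after surgery.

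**Inputs assumed.** The grade distributions. A mid-scale baseline has 5, 15, 30, 30, 20% in grades 1 to 5; a high-grade baseline has 2, 8, 20, 40, 30%. The other group (the group of 7 in the 7:5 case) is shifted by 2 on the log cumulative-odds scale, an odds ratio of e² = 7.4. For example, the mid-scale cumulative 5% has logit −2.94; subtracting 2 gives −4.94, or 0.7%. The shifted distributions are:

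- mid-scale, shifted up: 0.7, 2.6, 8.6, 23.2, 64.9%
- high-grade, shifted down: 13.1, 32.0, 30.9, 18.5, 5.5%
- high-grade, shifted up: 0.3, 1.2, 4.0, 18.5, 76.0%

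**Step 1: power for Landry grades.** Every possible 2×5 table was enumerated, its P value found under each test, and the probabilities of tables with P<.05 added up.

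| Scenario | Sizes | Fisher | Chi-square | Exact rank test |
|---|---|---|---|---|
| No difference (mid-scale) | 7:7 | 0.034 | 0.028 | 0.033 |
| No difference (mid-scale) | 7:5 | 0.032 | 0.026 | 0.033 |
| Mid-scale, up, odds ratio 2.7 | 7:7 | 0.078 | 0.070 | 0.119 |
| Mid-scale, up, odds ratio 2.7 | 7:5 | 0.077 | 0.064 | 0.110 |
| Mid-scale, up, odds ratio 7.4 | 7:7 | 0.262 | 0.231 | 0.367 |
| Mid-scale, up, odds ratio 7.4 | 7:5 | 0.277 | 0.215 | 0.328 |
| High-grade, down, odds ratio 7.4 | 7:7 | 0.200 | 0.169 | 0.407 |
| High-grade, down, odds ratio 7.4 | 7:5 | 0.139 | 0.118 | 0.337 |
| High-grade, up, odds ratio 7.4 | 7:7 | 0.243 | 0.222 | 0.276 |
| High-grade, up, odds ratio 7.4 | 7:5 | 0.273 | 0.222 | 0.269 |

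Under a larger assumed contrast (2, 5, 13, 35, 45% against 15, 30, 30, 20, 5%, cumulative odds ratios of about 9 to 16), Fisher gives 0.33 against 0.59 at 7:7, and 0.28 against 0.51 at 7:5.

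The first two rows show that the nominal tests do not inflate error. The last two show a limit: when about three-quarters of one group sit in the top grade, there is little order left to use and the advantage over Fisher disappears.

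**Step 2: GEE group effect at 7:7, by hand.** With complete visits, the group effect is a difference in patient averages. The uncorrected sandwich variance of a group mean is Σr²/n², where r is the residual of a patient's average. The unbiased form is Σr²/[n(n−1)]. The ratio is (n−1)/n = 6/7. So |z|>1.96 is the same as |t|>1.96×√(6/7) = 1.815 on 12 degrees of freedom, which under normality has probability 0.095.

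A Mancl-DeRouen correction divides each residual by 1−1/n, so the variance ratio becomes 7/6. With the normal cut-off, 1.96×√(7/6) = 2.117 gives 0.056. With the t cut-off, 2.179×√(7/6) = 2.353 gives 0.036.

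**Step 3: joint group-by-time Wald test at 7:7.** For k contrasts, W = (7/6)T², and T² follows [12k/(13−k)]·F(k, 13−k).

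- Four visits, k = 3: 7.815×6/7 = 6.698; F = 6.698×10/36 = 1.861; probability 0.200.
- Five visits, k = 4: 9.488×6/7 = 8.132; F = 8.132×9/48 = 1.525; probability 0.275.

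**Step 4: simulation with five-grade data under the null** (4 or 5 visits, latent correlation 0.3 to 0.7, uncorrected sandwich):

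- Group effect: about 9 to 10% at 7:7 and 10 to 12% at 7:5.
- Joint group-by-time test: about 20 to 28% at 7:7 and 25 to 36% at 7:5.
- Group effect with bias-reduced standard errors (4 visits, correlation 0.5): 5.6% at 7:7 and 6.1% at 7:5 with a normal reference. In a five-visit run with a t reference on n−2 degrees of freedom: about 4% at both sizes.

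**The case against.** The best defence is that the article names GEE but fixes neither a variance estimator nor a joint group-by-time test, and that such detail usually belongs in the analysis plan. This stands. A reader might infer that every longitudinal result from the fallback has an inflated error rate; the article does not support that. The inflation applies only if the usual uncorrected standard errors are used, and the largest figures only if a joint test is run. What is wrong whatever the estimator is the label: GEE is not a nonparametric method.

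A reader might also infer that all three choices both lose power and inflate false positives. They do not. The nominal tests lose power only. The normality check on the stability score shows no demonstrated harm, because Mann-Whitney is already its fallback. Simulating that two-stage rule on five-grade null data gave type I error of 4.3 to 4.7% at 7:7 and 3.6 to 4.5% at 7:5. Under the larger contrast in Step 1 its power was 0.63 and 0.52, against 0.62 and 0.49 for always using the asymptotic Mann-Whitney test. The case for one test on both scales is consistency.

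Finally, both scales are listed as secondary, the assumed distributions are not the trial's, and the rank test stays well below 80% power in every setting shown. All true, and they limit the weight of the point. They do not justify discarding the order, since the article itself names the tests for Landry grades and leaves no later choice open there.

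**Conclusion.** The point holds in two limited parts.

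1. Testing Landry grades as unordered categories loses power and nothing else. At an assumed odds ratio of 7.4, Fisher reaches about 0.14 to 0.28 and the exact rank test 0.33 to 0.41 in the two main scenarios. The difference is about 0.03 to 0.04 at odds ratio 2.7. It is nil or negligible where most patients reach the top grade. These sizes depend on proportional-odds shifts and baselines that the article does not supply.
2. GEE is wrongly described as nonparametric. If used with uncorrected sandwich standard errors at 12 to 14 patients, its type I error is about 9 to 12% for the group effect and about 20 to 36% for a joint group-by-time test, against 5%. A bias-corrected covariance nearly removes this for the group effect.

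The change is worth making because it is almost free. It does not rescue a study of this size from low power.

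**What to change.** In Statistical Analysis:

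- Move Landry grades out of the categorical list. Compare them with the exact Wilcoxon-Mann-Whitney test at a named visit, and report the probability index (the chance that a patient in one group has a better grade than a patient in the other, ties counted half) with a 95% CI.
- Use the same test for the five-point stability score, so that the two scales are handled alike. Keep chi-square or Fisher for arch form.
- Delete the description of GEE as nonparametric. For repeated grades, specify GEE with a bias-corrected (Mancl-DeRouen type) covariance and a t or F reference, or a rank or permutation method.
- Where a mixed model with Kenward-Roger degrees of freedom is wanted, confine it to gap width, which is continuous. It does not suit the five-point scales.

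The cost is wording; standard R packages cover these methods, and no extra patients or visits are needed. Longitudinal confidence intervals will be wider. The change should be dated and recorded before any between-group comparison is examined.

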**Methods:**

This prospective observational study is being conducted at the Department of Oral and Maxillofacial Surgery, Siddharth Gupta Memorial Cancer Hospital, in collaboration with the Sharad Pawar Dental College in Maharashtra, India. Patients aged 9 to 25 years with unilateral alveolar clefts measuring 1 cm or greater will be included. Patients with smaller clefts, bilateral clefts, or those who are unsuitable for surgery will be excluded. The study will evaluate 14 patients, divided into 2 groups: group A will undergo dentoalveolar transport distraction, whereas group B will undergo unilateral Le Fort I advancement. We will assess the closure of the alveolar gap, arch form, stability of the advanced or distracted segment, and soft tissue healing. Through cone beam computed tomography and maxillary occlusal view, radiographic parameters of closure of the alveolar gap and arch form will be evaluated. The outcome measures will be statistically analyzed on RStudio software, with appropriate tests applied to each outcome measure. *P*<.05 will be considered significant.

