### Outcome Measures and Data Collection

Data collection will occur at predefined intervals: preoperatively; immediately after surgery; and at 1, 3, 6, and 12 months of follow-up.

The following outcome variables will be systematically evaluated in both groups:

Alveolar gap closure will be measured radiographically using cone beam computed tomography (CBCT) at each interval.Maxillary arch form will be classified (U-shaped, V-shaped, or asymmetrical) using dental models and occlusal views.Segment stability will be assessed clinically and via CBCT using the 5-point bone stability scale.Soft tissue healing will be evaluated by blinded assessors using the Landry wound healing scale.

All CBCT images will be anonymized and randomized. Two independent evaluators, blinded to group assignment, will perform measurements. If visible hardware reveals the treatment allocation, a second reviewer re-evaluated the image independently.

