### Secondary Objectives

The secondary objectives will be to assess the intragroup outcomes over time for each technique and to evaluate patient-specific variables (eg, age and cleft width) that may influence outcome variation.

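### For gap width, a repeated-measures test over all listed visits is driven by closure itself and by when each technique closes the gap, so it says little about whether closure holds

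*Protocol article*

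**What the plan says.** The Statistical Analysis section names one approach for repeated data: "Longitudinal outcomes (eg, segment stability across time points) will be analyzed using repeated measures ANOVA for normally distributed data", and otherwise "generalized estimating equations for nonparametric repeated measures". Significance is P<.05, and 95% CIs are promised for all outcome measures.

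Secondary Objectives commits the study to "assess the intragroup outcomes over time for each technique". Outcome Measures and Data Collection sets the visits: "Data collection will occur at predefined intervals: preoperatively; immediately after surgery; and at 1, 3, 6, and 12 months of follow-up". For the gap it adds: "Alveolar gap closure will be measured radiographically using cone beam computed tomography (CBCT) at each interval". Primary Outcome lists the same visits, including the preoperative one, for gap closure.

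The abstract's Methods fixes the starting width: "unilateral alveolar clefts measuring 1 cm or greater will be included". Results reports a mean of 1.5 cm (SD 0.34, range 1.0-2.1) in the 12 patients enrolled, 7 in the distraction group and 5 in the Le Fort I group.

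The two techniques close the gap at different times. Intervention Delivery and the section on the distraction group describe 5 to 7 days of latency, then 1 mm per day until closure. The section on the Le Fort I group describes repositioning and fixation during the operation.

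**The concern.** The null hypothesis of an overall time test is that the mean gap is the same at every visit in the model. If the preoperative visit is one of them, that null is false as soon as the operation does what it is meant to do. The test then confirms that the cleft was narrowed, which nobody doubts, and gives the same answer for closure that lasts and closure that is partly lost by 12 months.

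The between-group version has a second problem. At the immediate postoperative visit the Le Fort I gap has been moved and the distraction gap has not. A group-by-time term over all visits picks up that scheduling difference even if the techniques end in the same place. For a primary outcome, it could be reported as a difference in performance between the techniques.

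**Working it through.** **Reading the schedule.**

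| Visit | Distraction | Le Fort I |
|---|---|---|
| Preoperative | open, at least 10 mm | open, at least 10 mm |
| Immediately after surgery | still open (latency 5-7 days) | segment moved |
| 1 month | movement finished if uninterrupted | segment moved |
| 3, 6, 12 months | follow-up | follow-up |

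End of distraction = latency + width ÷ rate. Shortest: 5 + 10/1 = day 15. Longest on the enrolled range: 7 + 21/1 = day 28. The 1-month visit therefore falls after movement for every enrolled width, but with no margin at the wide end.

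**Inputs from the article.** Preoperative width 15 mm, SD 3.4 mm, truncated to 10-21 mm; n = 7 and n = 5; alpha 0.05; six visits. The article states no power or error rate for the longitudinal test, so there is no figure of its own to reproduce.

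**Assumed.** Measurement noise, residual gap and amount of relapse are not given, so they were varied.

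**Test statistic.** One-way within-group repeated-measures ANOVA, F = [SS(time)/(k − 1)] / [SS(residual)/((n − 1)(k − 1))] with k visits; degrees of freedom are multiplied by the Greenhouse-Geisser epsilon where noted.

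**Check 1: full closure, relapse of 0, 2 or 4 mm by 12 months (4,000 runs per cell).**
- All six visits: probability of significance 1.00 at n = 7 and n = 5, for residual SD 0.5 to 3 mm and for every amount of relapse. Even with the most conservative lower-bound degrees of freedom it is at least 0.95.
- Post-closure visits only (from 1 month for distraction, from the immediate visit for Le Fort I; uncorrected degrees of freedom):

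| Residual SD | No relapse | 2 mm: distraction n=7 / Le Fort I n=5 | 4 mm: distraction n=7 / Le Fort I n=5 |
|---|---|---|---|
| 1 mm | 0.05 | 0.76 / 0.66 | 0.98 / 0.94 |
| 2 mm | 0.05 | 0.28 / 0.23 | 0.75 / 0.65 |

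**Check 2: 10% residual gap that holds, or relapses to 25% or 50% of original width (Greenhouse-Geisser, 2,000 runs, distraction gap open at the immediate visit).**
- All six visits, noise SD 0.7-2 mm: 100% rejection in both groups in all three scenarios.
- Visits from 1 month, noise SD 0.7 mm: about 2% when closure holds; 99% (n = 7) and 90% (n = 5) with relapse to 25%; 100% with relapse to 50%.

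**Check 3: group-by-time, both groups identical from 1 month on (10% residual, held).**
- All six visits: 100% rejection.
- Visits from 1 month: 2-4%.

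**Where the result weakens.**
- Half the gap remaining, SD 3 mm, n = 5: six-visit rejection is 0.86-0.91 uncorrected and 0.61-0.72 with Greenhouse-Geisser.
- 30% closure, SD 2 mm, n = 5: about 0.61-0.65 with Greenhouse-Geisser.
- 20% closure, SD 3 mm, n = 5: about 0.22-0.36 uncorrected.

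**The case against.** The strongest reply is that the article never says this analysis will be run. It does not state that the preoperative value enters the repeated response, that only the overall test will be read, or that no contrasts follow. Choice of contrast and reference visit is often left to a fuller document, and this is a condensed article. That stands as a limit. The point rests on the plain reading of the named method on the listed schedule, and the absence of contrasts is not itself the finding. What remains is that the method and schedule the article does fix do not, taken together, answer the stated question for gap width.

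The example in the quoted sentence is segment stability. A reader might infer that the stability score has the same defect. The documents do not support that: the 1 cm floor has no bearing on a 1-5 grade, and no passage clearly requires a preoperative score for a segment that has not yet been cut. That sentence does give stability only as an example, though, and the same section treats cleft width as a continuous outcome.

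It can also be said that the within-group objective does not mention maintenance, that whether the gap closed is a fair question, and that long-term relapse is assigned to future research in the Discussion. This is fair, but closure is better answered by an estimate with a CI, and follow-up to 12 months is within this study.

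Some protection exists already. Initial cleft width is a named covariate, 95% CIs are promised, and generalized estimating equations can give visit-level estimates. These help description. An overall time test from generalized estimating equations over the same visits has the same null, however, and the covariate does not remove the open-gap visits from the response.

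Finally, simply using the first postoperative visit as reference would not work for distraction. The gap is still open then, and in simulation perfectly held closure is flagged in 100% of runs. This objection stands and shapes the fix.

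**Conclusion.** The point holds for gap width, in conditional form. If all listed visits enter the repeated-measures model and closure is substantial, the overall time effect is significant almost regardless of whether closure holds or relapses (1.00 with full closure across the noise range tried). Over the same visits, the group-by-time term detects the difference in closure timing even when later results are identical (100% against 2-4% over visits from 1 month).

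A reader might go further and say that significance is certain whatever happens after surgery. That is not supported: with small closure and noisy measurement the rejection rate falls well below 1. The noise, residual and relapse values are assumptions throughout.

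The single-time between-group comparisons in the Statistical Analysis section are not affected. The consequence is confined to the longitudinal analysis of a primary outcome and the intragroup secondary objective. It should be corrected before results are examined.

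**What to change.** In Statistical Analysis, add for gap width:
- Restrict the repeated response to visits after movement is complete in both groups, and enter preoperative width as a covariate.
- For the intragroup objective, make the change from a common post-movement visit to 12 months the contrast, with its 95% CI.
- For the comparison of techniques, use the group-by-time term, or the between-group difference in that change, over the same visits.
- Use 1 month as the reference if distraction is complete by then in every patient (day 28 at the latest on the article's own figures, with no margin); otherwise use 3 months. Decide this from the distraction records, before outcomes are examined.
- Report preoperative-to-postoperative change as an estimate with a CI.

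This costs wording only: no new visits, scans or patients. The preoperative and immediate visits leave the repeated-measures test (the 1-month visit too if 3 months is the reference), and relapse before the reference visit is not captured by it. With 5 to 7 patients per group, modest relapse may still be missed (0.23-0.28 for 2 mm at residual SD 2 mm), so the CI should carry the interpretation.
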